### Hypothesis and objectives

#### Primary hypothesis

We hypothesise that point-of-care digital lung auscultation and LUS have a clinically exploitable predictive performance for the detection of pathological acoustic and sonographic signatures in patients with ILD. Furthermore, we propose that these signatures are sufficiently unique to not only discriminate ILD patients from control subjects, but also from COPD and other respiratory diseases, and perhaps even to categorise the various severity grades and subtypes of ILD, when determined. We further hypothesise that the automated interpretation of lung auscultation and LUS by deep learning could match or outperform expert evaluation and standardise lung auscultation and LUS interpretation.

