### Primary and secondary outcomes

The primary outcome is the diagnostic of ILD, both IPF and NSIP, versus control subjects or COPD. We will assess the predictive performance of the *DeepBreath* algorithm-evaluated lung auscultation and LUS in the following identification and risk stratification tasks as follows: (1) to discriminate ILD from control subjects (according to expert clinical diagnosis [42]); (2) to differentiate ILD from COPD; (3) to predict ILD clinical severity (according to a HRCT grading scale^1^ and lung function tests^2^); and (4) to differentiate the subcategories of ILD (such as IPF, NSIP) according to the gold standard diagnosis [2, 43, 44]).

Secondary outcomes are the clinical, functional and radiological characteristics of IPF, NSIP and COPD diagnosis. We will: (1) compare the predictive performance of human, expert-identified acoustic and LUS signatures in the above predictive tasks (Kappa coefficient); (2) assess diagnostic performance of a model trained to detect crackles; (3) explore the utility of adding clinical data (signs, symptoms, demographics, medical history and basic paraclinical tests) to the breath sound algorithms; and (4) determine the impact of the diseases on subjects’ health-related quality of life measured with the standardised King’s Brief Interstitial Lung Disease (K-BILD) [47], the COPD assessment test (CAT) [48], and the 36-item Medical Outcomes Study Short-Form Health Survey (SF-36) [49] severity assessment questionnaires.

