## AI algorithms

### Diagnostic and risk stratification algorithms

We will develop *DeepBreath*, a deep learning algorithm to detect the acoustic signatures of IPF, NSIP and COPD from lung sounds. While several state-of-the-art approaches will be tested, the general framework is summarised in Fig. 2. Digital lung auscultations will first be cleaned to crop non-biological frequencies and amplitudes generated by ambient noise not filtered by the stethoscope’s active noise cancelling. The sounds will then be divided into overlapping time windows of between 1 and 10 s and transformed to Mel Frequency Cepstral Coefficients (MFCCs). Several data augmentation techniques will be explored, such as amplitude scaling, pitch shift and random time shift. The effect of each pre-processing method will be tested and the best performing approach according to sensitivity and specificity will be reported. This dataset will then be fed into various deep learning networks (such as convolutional neural networks, Long Short-Term Memory models [LSTM], Transformer architectures, etc.). A prediction on each segment will then be aggregated to represent a patient (including all anatomic sites) and binary classification into positive *vs* negative for diagnostic results will be performed for ILD or control subjects, ILD or COPD, and (if ILD-positive) IPF or NSIP. The same prediction will also be made using LUS images. Risk stratification will use multiclass or regression according to scales obtained from clinical interpretation of LUS, lung function tests, HRCT imagery, K-BILD or CAT, and SF-36 quality of life questionnaires.

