## Clinical assessment of lung auscultation and LUS

The following data will be reviewed by external experts and interpreted using standardised report forms noting the binary presence/absence of several anomalies as well as a text field for other notable observations: routine chest X-ray films (usually 2 incidences, posterior-anterior and lateral); lung auscultation audio clips (10 anatomic regions represented, 30 s recordings of each region); and LUS images (10 anatomic regions represented, 5 s video clips of each region). The analysis will be blinded and the assessor will not have any knowledge of the linked clinical data or association between the various imaging modalities (i.e., IDs are scrambled between media sources and chest X-ray images will be reviewed blinded to the patient’s LUS images, auscultation audio, clinical data, etc.). These blinding and standardisation procedures are expected to minimise performer and study management bias respectively.

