### Statistical analysis plan

For descriptive statistics related to the clinical data collected, all continuous variables will be reported as medians with their interquartile ranges. Binary and categorical variables distribution will be reported as proportions and percentages. To evaluate baseline demographic differences and outcomes differences between the case and control patients, conditional logistic regressions will be used to account for the matched design. Pearson’s and Spearman’s correlation coefficients will be used to assess the relationship between continuous variables normally and non-normally distributed, respectively. For the primary outcome, each task will be quantified using descriptive statistics (i.e., proportion and type of abnormalities), as well as the AUROC, sensitivity, specificity, positive predictive value, negative predictive value, and likelihood ratios (with 95% CIs over a fivefold cross-validation).

The diagnostic accuracy of each echographic sign will be assessed and sensitivity, specificity, positive predictive value, negative predictive value, positive likelihood ratio, and negative likelihood ratio with their 95% CIs will be calculated. To find the combination of echographic signs with the best diagnostic accuracy, we will compare the performance of several multivariable models, such as logistic regression, random forest and neural networks. Performance will be reported on a test set comprising 20% of the data in a tenfold cross-validation with 95% CIs. As a secondary objective, we will aim to compare the predictive performance of human expert-identified acoustic signatures in the above predictive tasks. First, we will describe the expert labels by the percentage of sound labels attributed to each diagnosis. A multivariable logistic regression will be derived using the clinical data and sound labels to estimate the diagnoses, as for the primary objective. A kappa score will be used to assess the concordance between *DeepBreath* and expert diagnosis consolidated into a basic predictive model.

The K-BILD, CAT and SF-36 questionnaires will be analysed with descriptive statistics. Associations between the questionnaires’ sum scores and lung function parameters will be quantified by Spearman’s rank correlation coefficient. We will consider correlations < 0.3 as negligible, ≥ 0.3 to < 0.5 as low, ≥ 0.5 to 0.7 as moderate, and ≥ 0.7 as strong.

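### The expert sound comparator includes clinical data that DeepBreath, as defined, does not use, so a tie, a loss or low agreement could not be read as a comparison with expert auscultation

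*Protocol article*

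**What the plan says.** The Primary hypothesis section of the protocol article proposes that "automated interpretation of lung auscultation and LUS by deep learning could match or outperform expert evaluation". Under Primary and secondary outcomes, the first secondary item is to compare the predictive performance of expert-identified acoustic and LUS signatures on the primary tasks, with kappa as the named statistic.

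Under Clinical assessment of lung auscultation and LUS, experts label the clips blinded: "the assessor will not have any knowledge of the linked clinical data".

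The Statistical analysis plan section first tabulates expert labels by diagnosis and then fixes the model: "A multivariable logistic regression will be derived using the clinical data and sound labels to estimate the diagnoses, as for the primary objective". The next sentence reads: "A kappa score will be used to assess the concordance between *DeepBreath* and expert diagnosis consolidated into a basic predictive model".

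The Diagnostic and risk stratification algorithms section describes DeepBreath as "a deep learning algorithm to detect the acoustic signatures of IPF, NSIP and COPD from lung sounds", and says the same prediction will be made from LUS images. Clinical data join the sound algorithm only in a separate exploration (third secondary item, and the section on synergy of clinical data with breath sounds).

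**The concern.** The question is whether a machine reads lung sounds as well as an expert does. Both sides should then work from the same signal. As written, the expert side has the signal plus clinical data, and DeepBreath as defined has the signal without them. The protocol's own list of clinical data covers signs, symptoms, demographics, history and basic paraclinical tests, all of which may separate the groups whatever the listener hears.

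If the expert model then equals or beats DeepBreath, or the two disagree, the cause could be the clinical variables. The secondary aim concerns the performance of acoustic signatures identified by experts, and no expert sound model isolates it. The part of the primary hypothesis about matching experts is affected in the same way.

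**Working it through.** The protocol gives no power, margin or expected value for this comparison, so there is no figure to reproduce. The check sets out the inputs of each model and then illustrates the possible size.

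**Inputs of each model**

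| Model | Signal | Clinical data | Where in the protocol article |
|---|---|---|---|
| Expert sound model | Expert sound labels | Yes | Statistical analysis plan |
| DeepBreath, audio | Lung sounds | No | AI algorithms; Fig. 2 legend |
| LUS-image prediction | LUS images | None named | AI algorithms |
| Echographic-sign models | LUS signs | None named | Statistical analysis plan |
| DeepBreath plus clinical data | Lung sounds | Yes | Outcomes; synergy section |

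The table has no model on expert sound labels alone. The last row would match the first, but the kappa sentence does not name it.

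**Illustrative size.** Assume two binormal predictors with equal variances, within-class correlation ρ and optimal linear combination. None of the AUROC values in this step comes from the protocol.

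- Separation: d = √2 × Φ⁻¹(AUROC). For labels alone at 0.80, d₁ = 1.190. For clinical data at 0.70, 0.75 and 0.85, d₂ = 0.742, 0.954 and 1.466.
- Combined: D² = (d₁² + d₂² − 2ρd₁d₂)/(1 − ρ²), and AUROC = Φ(D/√2).

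| Clinical data alone | ρ = 0: D | ρ = 0: AUROC | ρ = 0.3: D | ρ = 0.3: AUROC |
|---|---|---|---|---|
| 0.70 | 1.402 | 0.839 | 1.257 | 0.813 |
| 0.75 | 1.525 | 0.860 | 1.345 | 0.829 |
| 0.85 | 1.888 | 0.909 | 1.664 | 0.880 |

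The lift over 0.80 runs from 0.813 − 0.80 = 0.013 to 0.909 − 0.80 = 0.109, or about 0.01 to 0.11.

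Take a DeepBreath audio model with a true AUROC of 0.83, which is better than the labels. At ρ = 0 it would appear worse than the comparator by about 0.01 to 0.08. At ρ = 0.3 it would be ahead of 0.813, level with 0.829 and behind 0.880. The sign of the apparent difference therefore depends on the clinical data.

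**The protocol's own crackle figures.** The Sample size calculation section expects velcro-like crackles in nearly 100% of IIP patients and, by definition, no pathological sounds in controls. For a binary label, AUROC = (sensitivity + specificity)/2.

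- ILD versus control: (1 + 1)/2 = 1.00, so clinical data have almost nothing to add.
- IPF versus NSIP, on presence of velcro-like crackles alone: (1 + 0)/2 = 0.50, so beyond that label any discrimination would come from other labels or from clinical data.

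**What kappa can show.** Assume sensitivity equals specificity, errors are independent within class, and prevalence is 80/120 (80 ILD, 40 controls). With accuracies of 0.95 for DeepBreath and 0.80 for the expert model:

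- observed agreement = 0.95 × 0.80 + 0.05 × 0.20 = 0.77
- positive-call rates = 0.65 and 0.60
- chance agreement = 0.65 × 0.60 + 0.35 × 0.40 = 0.53
- kappa = (0.77 − 0.53)/(1 − 0.53) = 0.51

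Swapping the two accuracies also gives 0.51. Kappa does not say which side is better. That is a separate matter, and another statistic would leave the unequal inputs in place.

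**The case against.** **The pairing is inferred.** The kappa sentence refers to "expert diagnosis consolidated into a basic predictive model" without stating that this is the regression in the sentence before it, and it does not say which DeepBreath version is meant. The full analysis plan may settle this. This stands as a qualification. However, the article does fix the inputs of the only expert sound model it describes, and no other candidate appears.

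**DeepBreath may not be sound-only.** The Abstract has it trained on audio and LUS images, and the outcomes section speaks of DeepBreath-evaluated auscultation and LUS. On that reading DeepBreath holds LUS information that the expert sound model lacks, and the imbalance need not favour the expert. This stands. The inputs remain unequal, but the direction of the advantage is less certain.

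**LUS is largely covered.** The plan already assesses each echographic sign and models their combinations without naming clinical data. This stands, and the gap is in the sound comparison.

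**Stronger readings.** A reader might infer that the comparison can answer nothing in either direction. It can: if sound-only DeepBreath clearly outperformed a well-fitted comparator holding more information, that would support outperformance all the more. A reader might also infer that the regression undoes the blinding of the experts. It does not. The labels are assigned blind and stay so; what is missing is an analysis of those labels by themselves.

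**The stakes are modest.** This is a secondary objective in a self-described pilot, and the output will not guide care. That limits the weight of the point. It still bears on a stated hypothesis.

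**Conclusion.** The point holds in limited form. The expert-side sound model combines clinical data with sound labels, DeepBreath as defined has no clinical data, and no label-only sound model is specified. A tie, a loss or low kappa could not be attributed to how well experts read the sounds. The secondary aim on expert-identified acoustic signatures, and the matching part of the hypothesis, are therefore not cleanly tested. A clear DeepBreath win on performance measures would remain informative, barring an overfitted comparator.

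This rests on reading the regression as the model entering the kappa, and on DeepBreath being the version without clinical data. The lift of about 0.01 to 0.11 AUROC assumes a label-only value of 0.80, clinical data at 0.70 to 0.85, and a within-class correlation of 0 to 0.3. It illustrates scale and does not predict the result. On the protocol's crackle prevalences it would be close to zero for ILD versus control, so the point matters mainly for harder tasks such as IPF versus NSIP.

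**What to change.** In the Statistical analysis plan section:

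- Add a logistic model on expert sound labels alone, and compare it with audio-only DeepBreath in the same patients and folds.
- Pair the already planned echographic-sign models with the LUS-image model in the same folds.
- Compare labels plus clinical data only with DeepBreath plus the same clinical variables.
- State which DeepBreath version enters each comparison, and base any statement about matching or outperforming experts on the same-modality comparisons.

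The cost is a change of wording, one or two extra fits on data already planned, and a few more comparisons to report. No additional patients, readers or procedures are needed.

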### Sample size calculation

Each patient will provide 10 audio recordings of 30 s. Samples will be considered at the patient level with all 10 recordings. In deep learning, sample size calculation is an intractable problem that is usually discovered through empirical investigation. The number of samples required to reach a certain performance criterion is dependent on the characteristics of the dataset, the diversity and number of the classes, the degree of data augmentation possible, as well as the complexity of the learning algorithm. Thus, sample size calculations cannot rely on the traditional statistical heuristics that are often used in biostatistics. Rather, sample size estimations in deep learning are mostly made by analogy. Evaluating existing knowledge on similar datasets, we find that the expected proportion of velcro-like crackles in IIP patients is nearly 100% [4], whereas the prevalence of coarse crackles is 71% in COPD patients [58]. The exclusivity of these sounds among groups is not known, but overlap is assumed to be minimal and pathological sounds are by definition absent in non-ILD and non-COPD control subjects. Assuming a similar discriminative power compared to a previous work done by our group (personal communication) to distinguish between normal and pathological lung sounds in pneumonia from 80 patients in balanced classes (40 pathological; 40 controls) with 8 auscultation sites of 30 secs each, we estimate using the same number of patients in each class to achieve convergence at above 80% of the area under the receiver operating characteristic curve (AUROC). Thus, we will aim to enrol at least as many patients in each group: 80 ILD (40 IPF, 40 NSIP); 40 COPD; and 40 controls (i.e., known not to have ILD or COPD, and with normal lung function). As the recruitment site would expect 120 ILD patients (40% with IPF; 60% with NSIP) and 100 with COPD over the space of one year, this number is achievable in the time frame of the study (6 months), even with a 70% consent rate.

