Missing data will be reported and padded with zero in the deep learning network and also assessed according to other labels. Features with more than 50% missing values or with a significant bias in missing data fields will be removed and reported. All statistical tests will be two-sided with a type-I error risk of 5%. Data analysis will be carried out using the latest version of R (R Foundation, Vienna, Austria) for descriptive statistics and statistical tests.

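### Kappa is the statistic assigned to comparing DeepBreath with experts, but it measures agreement and cannot show which of the two is more accurate

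*Protocol article*

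**What the plan says.** Four places in the protocol article bear on this point.

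- **Primary hypothesis.** Its last part is that deep-learning interpretation "could match or outperform expert evaluation and standardise lung auscultation and LUS interpretation".
- **Primary and secondary outcomes.** Secondary outcome (1) is to "compare the predictive performance of human, expert-identified acoustic and LUS signatures in the above predictive tasks (Kappa coefficient". The parenthesis names no other statistic.
- **Statistical analysis plan, expert comparison.** The aim is repeated, for sounds only: "we will aim to compare the predictive performance of human expert-identified acoustic signatures in the above predictive tasks". Three steps follow. Expert labels are described as percentages by diagnosis. Then "A multivariable logistic regression will be derived using the clinical data and sound labels to estimate the diagnoses, as for the primary objective". Finally, "A kappa score will be used to assess the concordance between" DeepBreath and the expert diagnosis, the latter condensed into a simple predictive model.
- **Statistical analysis plan, accuracy measures.** Each primary-outcome task is to be quantified by descriptive statistics "as well as the AUROC, sensitivity, specificity, positive predictive value, negative predictive value, and likelihood ratios", with 95% CIs over fivefold cross-validation. Individual echographic signs also get accuracy measures with 95% CIs.

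The article states no difference in accuracy between DeepBreath and experts, no interval for one, no target kappa, and no margin for what counts as a match.

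**The concern.** Matching or outperforming is a statement about two error rates, each measured against the true diagnosis. Kappa between DeepBreath and the expert-based model compares their calls only with each other. Swapping the two leaves it unchanged, and the reference diagnosis does not enter the formula. A high value may mean that both are accurate or that both make the same mistakes. A moderate value may mean that DeepBreath is better, worse or equal. If DeepBreath really is more accurate than the experts, the two must disagree on some patients and kappa must fall below 1, so reading high agreement as success works against the hypothesis.

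At stake are a secondary outcome and the last part of the primary hypothesis. The accuracy measures for the primary outcome are not affected.

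**Working it through.** The article gives no figure for this analysis, so there is none to reproduce. The check is whether kappa can tell apart the situations that the hypothesis distinguishes.

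**Inputs.** Group sizes come from Sample size calculation: "80 ILD (40 IPF, 40 NSIP); 40 COPD; and 40 controls". ILD versus controls is therefore 80 v 40, with an ILD fraction of 2/3. The sensitivities, specificities and error overlap are assumptions, because the article gives none.

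**Formula.** Kappa = (po − pe)/(1 − pe), where po is observed agreement and pe is the agreement expected from the two proportions of positive calls.

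**One classifier at Se = Sp = 0.90, the other at 0.70**
- Positive calls: (2/3)(0.90) + (1/3)(0.10) = 0.6333 and (2/3)(0.70) + (1/3)(0.30) = 0.5667.
- pe = 0.6333 × 0.5667 + 0.3667 × 0.4333 = 0.5178.
- Independent errors within each diagnosis: po = 0.90 × 0.70 + 0.10 × 0.30 = 0.66, so kappa = 0.1422/0.4822 = 0.295.
- Nested errors (the better classifier's errors are all shared by the worse): the counts are 60 both positive, 36 both negative and 24 discordant. Then po = 96/120 = 0.80 and kappa = 0.2822/0.4822 = 0.585.
- Exchanging DeepBreath and the experts changes none of these values.

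**Both at Se = Sp = 0.80**
- Positive calls are 0.60 for each, so pe = 0.36 + 0.16 = 0.52.
- Independent errors: po = 0.64 + 0.04 = 0.68, so kappa = 0.16/0.48 = 0.333.
- Half of each classifier's errors shared: po = 96/120 = 0.80, so kappa = 0.28/0.48 = 0.583.
- All errors shared: po = 1 and kappa = 1.

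**Both at Se = Sp = 0.50 with identical calls:** kappa = 1, the same as for two perfect classifiers.

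| Situation | Kappa |
|---|---|
| DeepBreath 0.90, experts 0.70 | 0.295 (independent) to 0.585 (nested) |
| DeepBreath 0.70, experts 0.90 | 0.295 (independent) to 0.585 (nested) |
| Both 0.80 | 0.333 (independent), 0.583 (half shared), 1 (all shared) |
| Both 0.50, identical calls | 1 |

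A paired comparison against the diagnosis does separate them. In the nested 0.90 v 0.70 table, all 24 discordant patients favour the better classifier (exact McNemar p = 2 × 0.5^24 = 1.2 × 10⁻⁷). In the equal case with half of the errors shared, the discordant patients split 12 to 12 (p = 1).

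**Precision of a paired AUROC difference.** Assume both AUROCs are 0.80. The Hanley-McNeil SE is 0.0397 for 80 v 40 and 0.0498 for 40 v 40 (IPF versus NSIP). The SE of the difference is SE × √(2(1 − r)), with the correlation r assumed between 0 and 0.7.
- 80 v 40: 95% half-width 1.96 × 0.0397 × √2 = 0.110 at r = 0, and 1.96 × 0.0397 × √0.6 = 0.060 at r = 0.7.
- 40 v 40: 0.138 and 0.076 by the same steps.

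**The case against.** The strongest defence has four parts.

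1. **Accuracy on both sides may be available.** The expert regression is derived to estimate the diagnoses in the same way as for the primary objective, which can be read as promising the same accuracy measures. Echographic signs are also evaluated against the diagnosis with CIs. This stands. A reader might infer that the match-or-outperform hypothesis cannot be examined at all under this plan. The document does not support that, because an informal side-by-side reading would be possible. Two separate intervals are still not an interval for the difference, and kappa remains the statistic named for the comparison.
2. **The kappa sentence speaks of concordance, which is what kappa measures.** Taken alone, that sentence is sound. The fault comes from the secondary outcome, which labels a comparison of predictive performance with kappa, and from the analysis section, which gives kappa under that same aim.
3. **Margins, tests and fold handling belong in a full analysis plan, and the study is described as a pilot.** Leaving out such detail would be no finding. Here, though, the article names a statistic, and it does not fit the stated purpose. The pilot status and the secondary rank of the outcome limit how much this matters.
4. **The kappa values depend on assumed error overlap.** Correct. A reader might take 0.295 as the expected result, but the same accuracies give 0.585 with nested errors. Only the symmetry, and the absence of the reference diagnosis from the formula, are general.

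**Conclusion.** The point holds in limited form. The article assigns an agreement statistic to a comparison of predictive performance and makes it the only direct DeepBreath-versus-expert analysis. That statistic cannot support a claim of matching or outperforming. Under the assumed accuracies, the ranges of kappa for a better, a worse and an equal DeepBreath overlap, and the better and worse cases are identical. This conclusion needs no assumption about accuracies or error dependence; only the illustrative values do.

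The plan should be corrected, but the defect is moderate. It touches a secondary outcome and one clause of the primary hypothesis, and side-by-side accuracy figures may soften it.

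**What to change.** In both Primary and secondary outcomes and Statistical analysis plan, define the comparison as the paired difference between DeepBreath and the expert-label model against the reference diagnosis:

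- the difference in AUROC, by DeLong or paired bootstrap, and the differences in sensitivity and in specificity, with McNemar comparisons, all with 95% CIs;
- both models evaluated on the same out-of-fold patients, with the expert-label model fitted in the same folds;
- matched inputs. The planned expert regression includes clinical data, while the core DeepBreath model uses sounds or LUS images alone, so an unmatched difference would mix reading skill with extra information. Compare sound or LUS labels alone with DeepBreath alone, and labels plus clinical data with DeepBreath plus clinical data;
- kappa kept as a descriptive measure of agreement only.

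The cost is a short rewording in two sections and a somewhat larger analysis. No data are needed beyond those already planned. The difference will be imprecise: the 95% half-width in AUROC is about 0.06 to 0.11 for 80 v 40 and 0.08 to 0.14 for 40 v 40, under the assumptions in the working. It should be reported as an estimate with its interval, not as a verdict on superiority or equivalence.
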